**Economic Opportunity for Zimbabwean Adolescent Orphans**

1. **Study Aims**

The overall aim of this project is to determine, using a randomized controlled design, whether a economic livelihood (in this case vocational training package including monthly fees, a modest stipend based on progression and performance in the training program, and a completion bonus) and life-skills intervention, designed to increase control over sexual interactions, prevents the adverse consequences of unprotected sex among out-of-school female orphans aged 16-19 in Zimbabwe compared with a life-skills intervention alone.

**Aim 1: To assess the effectiveness of a combined vocational training package and life-skills education intervention in reducing the incidence of our primary outcomes: Herpes simplex virustype 2 (HSV2) and unintended pregnancy.** Although not powered to assess HIV as an outcome, we will nevertheless monitor HIV incidence between groups. (Note that rates of bacterial STDs are too low to consider.) We hypothesize that compared to those in the control group, adolescent female orphans receiving the combined intervention will experience a lower incidence of these outcomes.

Aim 2: To assess the effectiveness of a combined vocational training package and life-skills education intervention in reducing our secondary outcomes: high-risk behaviors (e.g., unprotected sex, number of partners, transactional sex, early sexual debut, sexual coercion and violence). Our hypothesis is identical to that for Aim 1.

**Aim 3. To examine the intermediary effects of increased economic opportunity, social support, and improved sexual negotiation skills in enhancing participants’ control over sexual interactions.** We hypothesize that the combined intervention will enable participants to, for example, increase and gain control over their income and future income-earning potential (through the vocational training intervention), thereby empowering them to use the sexual negotiating skills gained through the life-skills intervention. Together, these outcomes will increase participants’ control over sexual activity, and reduce the prevalence of sexual risk behaviors and the incidence of both HSV-2 and unintended pregnancies. This aim will allow us to examine why the intervention is or is not effective. Furthermore, if the predictive value of these outcomes is high, this may obviate the need for collection of biological data and self-reports of sensitive behaviors in future studies.

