**2. Pilot Study Design**

We conducted a cross-sectional study among 200 in and out of school girls between 16 and 19 years of age living in our research sites. Convenience sampling was used to recruit participants into the study. Participants were enrolled at clinic locations in both sites, as well as through a mobile clinic facility. A subset of 50 orphans (defined as having lost at least one parent) was enrolled into the pilot intervention and was followed up at 3 and 6months.

Information at baseline and follow-up visits was collected from study participants using both quantitative and qualitative methods of data. Quantitative surveys, using face to face interviews and ACASI, were conducted at baseline, and at 3 and 6 months to collect information on demographics, HIV and RH knowledge, sexual behavior and contraceptive use, partners, relationship power and current economic activities. Biological specimens for HIV, HSV-2 and pregnancy were collected and tested. Qualitative data was collected through observation and in-depth interviews throughout the pilot to provide information on implementation quality and to assess successes and failures of the intervention. Process evaluation data on training attendance, loan disbursement, loan repayment, and business assessments were also collected. The main outcome variables assessed were socio-demographic characteristics, sexual behavior, control over sexual interactions, sexual and physical abuse, participation in and knowledge gained from training, micro-enterprise activities, including income generation, and HIV, HSV-2, and pregnancy status.

3. Findings

The pilot study cross sectional survey (n=200) showed that orphans and out of school girls were more likely to be sexually active (40% vs 24%), have a higher prevalence of HIV (9% vs 3%), HSV-2 (10% vs 6%) and to have had a past or current pregnancy (15% vs 5%). Among the 50 enrolled in the pilot intervention, 43% had ever had sex, 57% and 14% had ever used male and female condoms respectively and 14% had ever been raped. Fifty seven percent had been sexually active in the last three months and 44% received basic needs/money from primary sexual partner at baseline.

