Additional calculations for Aim 2 are based on comparing observed changes in self-reported behaviors between arms using a t-test with adjustment for within-group correlations as described above. For these calculations, we assume changes will be computed as binary indicators of decrease in risk-taking behavior between the initial and final visits (e.g., a decrease in self-reported unprotected sex, or in the annual number of sexual partners). We also assume that the background prevalence of individuals reporting a decrease in risk-taking behavior ranges between 10% and 50%, and that the between-cluster coefficient of variation in prevalence within arms is 0.2. With these assumptions, our planned sample size should provide 80% power to detect prevalence ratios comparing prevalence of behavior change in the combined intervention group to that in the control group in the range .55-.7 at the 5% significance level. This corresponds to absolute differences in prevalence between arms of .07 – x.15, indicating that we should have sufficient power to detect relatively small differences between groups for a range of observed changes in high-risk behaviors.

Formal sample size calculations are not presented for Aims 3 or 4 because detailed preliminary information on the joint distribution of behavioral (including characteristics of participation) and our primary and secondary outcomes do not exist, and because the analyses proposed for these aims (described in section D.11.) are exploratory in nature. Since these analyses may involve estimation of interactions, we will clearly have reduced power compared to the analyses for Aims 1 and 2. However, we anticipate that power will be adequate to detect important associations.

1.b. Sample Size – Qualitative Component

Adolescent Girl Participants: Forty main study participants (20 from the intervention arm and 20 from the control arm) will be selected for participation in the qualitative interviews. As participants are enrolled into either study arm, every 5th girl in both arms will be selected for participation. The 40 participants will be interviewed 3 times for the duration of the study for a total of 120 interviews.

Interviews from an additional 10 participants enrolled in the Prevention for Positives component (5 from each arm, randomly chosen from the new cohort of 50) will be added to explore the feasibility of the study to include and support HIV and HSV-2 positive participants.

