The effect of the combined intervention on reduction in self-reported risk behaviors (Aim 2) will be evaluated by comparison of the difference in average behavior change between arms. Changes will initially be computed as binary indicators of decrease in behavior between the initial and final visit, and results assessed via the between-arm difference in proportions. Similar to the approach described above for Aim 1, GEE methods will be used to account for potential correlations between outcomes within peer groups. We will compare absolute prevalence of risk behaviors at successive follow-up visits in a similar fashion.

The goal of Aim 3 will be to investigate the association between intermediary effects of the proximal outcomes of intervention and sexual negotiation skills as well as control over sexual interactions, in an effort to understand possible causal links. The analyses will focus on girls in the intervention arm. Intermediary outcomes will be quantified using a variety of measures, including successful completion of vocational training, utilization of social support /counseling, control over economic resources and decision making, self-efficacy and risk-related behavior (using economic modeling), future goals and aspirations.

Analyses of the relationship between characteristics of participation: adherence, satisfaction and understanding, to biological and behavioral outcomes (Aim 4) will be similar to those presented for Aim 3 and will focus on participants in the intervention arm. For example, adherence will be measured using visit-specific categorical and continuous summaries of participation in program activities (e.g. attendance at training sessions). These will be related as time-varying covariates to primary (biological) outcomes using discrete time survival analysis techniques as described for Aim 3. The approach for secondary (behavioral) outcomes will also be based on visit-specific indictors of current behavior, which will be related to adherence using GEE regression methods for binary outcomes. As before, we will control for membership in peer groups in the analyses.

For the qualitative component, data will be transcribed from audio tapes and translated, then entered into Atlas.ti for qualitative data analysis. The transcripts will be coded and themes identified that will be tabulated to help inform all aspects of the data analysis process.

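### The first-named and only powered Aim 2 indicator counts decreases alone, so it cannot register prevented onset or assess early sexual debut, and the plan does not say which analysis decides Aim 2

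*Protocol*

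**What the plan says.** Section 1 (Study Aims) lists the Aim 2 outcomes as "unprotected sex, number of partners, transactional sex, early sexual debut, sexual coercion and violence".

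Under Methods of Data Analysis, 2. Data Analysis, the Aim 2 paragraph compares behaviour change between arms: "Changes will initially be computed as binary indicators of decrease in behavior between the initial and final visit", with "results assessed via the between-arm difference in proportions" and GEE for correlation within peer groups. The same paragraph then adds: "We will compare absolute prevalence of risk behaviors at successive follow-up visits in a similar fashion". It does not rank the two analyses.

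The Aim 2 power statement under 1.a (Sample Size – Quantitative) rests on "binary indicators of decrease in risk-taking behavior between the initial and final visits". It assumes that 10% to 50% of girls report a decrease and that the between-cluster coefficient of variation is 0.2. It claims 80% power for prevalence ratios of .55 to .7, or absolute differences of .07 to .15. No power is given for follow-up prevalence.

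On baseline activity, the pilot findings (section 2.H) report: "Among the 50 enrolled in the pilot intervention, 43% had ever had sex". In the pilot survey of 200, 40% of orphans and out-of-school girls were sexually active. The main trial admits only girls who are HSV-2 negative, HIV negative and not pregnant.

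**The concern.** A decrease needs something to decrease from. For a girl with no unprotected sex, partners or transactional sex at baseline, the indicator takes the same value if she remains without risk and if she begins. It also does not separate a girl who escalates from one who stays the same. Early sexual debut can only be an onset, so no version of the indicator measures it.

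The participants are 16 to 19 at entry, are followed for about two years, and are screened free of both infections and of pregnancy. Preventing the start of risk behaviour is therefore one plausible way for the intervention to work, and the first-named measure is blind to it. If the decrease indicator and follow-up prevalence disagree, the plan gives no rule for which one answers Aim 2, and that choice could be made after the results are known.

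**Working it through.** **Inputs.** From the protocol: 150 per arm; groups of 25, so 6 clusters per arm; 20% loss, so 120 per arm or 6 clusters of 20; coefficient of variation k = 0.2; 43% ever had sex in the pilot. The 5% level is taken as two-sided.

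**1. The plan's own power figure.** It does not reproduce.
- At 10% background with ratio .55, the difference is 0.10 × (1 − 0.55) = 0.045, not .07. At 50% with ratio .7 it is 0.50 × (1 − 0.7) = 0.15, which agrees.
- The clustered variance of the difference in proportions (Hayes–Bennett) is [p0(1−p0)/m + p1(1−p1)/m + k²(p0² + p1²)]/(c − 1). With c = 6, m = 25 and 80% power, the detectable ratio is 0.15 at 10% background and 0.56 at 50%.
- At the stated ratios, power is about 25% (10% background, .55) and 44% (50% background, .7).
- Ratios below 1 for the share decreasing, intervention over control, would mean that fewer intervention girls reduce risk. The direction needs settling when power is restated.

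**2. Ceiling on the indicator.**
- If 43% have ever had sex: 0.43 × 150 = 64.5 per arm, or 0.43 × 120 = 51.6 retained.
- The pilot also says: "Fifty seven percent had been sexually active in the last three months". Its denominator is not given. Read as a share of the 43%, it is 0.57 × 0.43 = 24.5%, or about 37 of 150. Read as a share of all 50, it contradicts the 43%.
- A 50% background would need 0.50/0.43 = 116% of ever-active girls to decrease, which is impossible. A 10% background needs 0.10/0.43 = 23%, which is possible.
- Sampling error: 0.43 ± 1.96 × √(0.43 × 0.57/50) = 0.43 ± 0.137, about 29% to 57%.

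**3. Intervention acts on onset only** (assumed: 43% active at baseline; 40% of these stop in both arms; onset 50% control, 25% intervention).
- Decrease indicator: 0.43 × 0.40 = 17.2% in both arms, so no effect.
- Final prevalence: 0.43 × 0.60 + 0.57 × 0.50 = 54.3% control; 0.258 + 0.57 × 0.25 = 40.1% intervention. Power is about 60% unclustered with 120 per arm, and 34% with 6 clusters of 20 and k = 0.2.

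**4. Intervention acts on onset and persistence alike.** Let b be the share at risk at baseline, s the share of these still at risk, q the onset share and r the multiplier on follow-up risk. Decrease: b(1 − s) against b(1 − sr). Status: bs + (1 − b)q against r times that. Assume b = 0.25, s = 0.7, q = 0.25, r = 0.6.
- Decrease: 7.5% against 14.5%, unclustered power 41%.
- Status: 36.25% against 21.75%, unclustered power 71%.
- Over b of 15% to 43% and q of 15% to 35%: 26% to 67% for decrease, 46% to 90% for status.
- With k = 0.2 and 6 clusters of 20, the central case is 33% against 50%, or 38% against 58% when the variance is divided by c rather than c − 1.
- At b = 0.43 and q = 0.15, clustered (c − 1), it is 52% against 53%, practically no difference.

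**5. Intervention acts only on girls already at risk** (b = 0.43, q = 0.25, s = 0.7, r = 0.6).
- Decrease: 12.9% against 24.9%, unclustered power 67%.
- Status: 0.301 + 0.1425 = 44.4% against 0.1806 + 0.1425 = 32.3%, unclustered power 49%. The ranking reverses.

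**The case against.** A reader might infer that Aim 2 as a whole ignores new risk behaviour. The documents do not support that. The decrease indicator is described as an initial computation, and the same paragraph plans a comparison of prevalence at successive follow-up visits, which captures onset and uses every visit. What remains is that this second analysis has no power statement and that neither is named as decisive.

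A reader might also infer that most girls in the trial cannot score a decrease. That rests on 50 pilot girls drawn from a convenience sample of girls in and out of school. The protocol gives no baseline activity figure for the 315 enrolled, and the interval around 43% reaches 57%. The 10% to 50% range is a span of scenarios across behaviours, and its lower part is attainable. Coercion and violence need not presuppose earlier sexual activity.

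Nor does the protocol say that girls without a final visit are dropped. Handling of missing visits is properly left to an analysis plan.

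Finally, Aim 2 is worded as a reduction in behaviours, the outcomes are secondary, and the randomised comparison stays unbiased. The loss is of sensitivity, and step 5 shows that it can go the other way. All of this stands. It limits the size of the point but does not remove the blindness to onset or the mismatch with sexual debut.

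**Conclusion.** The point holds for the first-named indicator. By construction it scores onset and non-onset alike, and it cannot assess early sexual debut; neither statement needs any assumption. If the pilot's 43% carries over, fewer than half the girls could show a decrease in a behaviour that requires sex, and the top of the assumed background range is unattainable for those behaviours.

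The gain in power from switching measures is illustrative. It is large if onset is prevented, from negligible to moderate under clustering when onset and persistence are affected alike, and negative if only girls already at risk change. The documents do not say which pattern to expect. The case for change therefore rests on covering the listed outcomes and fixing in advance which analysis decides, more than on any one power figure. It is a worthwhile and inexpensive correction to a secondary aim; Aim 1 is unaffected.

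**What to change.** - Name the already planned comparison of follow-up prevalence as the leading Aim 2 analysis: GEE over the follow-up visits, allowing for peer group, adjusted for the baseline value of the same behaviour. The model details can sit in the analysis plan, but the choice of leading analysis should be in the protocol.
- Analyse sexual debut as onset among girls not sexually active at baseline.
- Keep the decrease indicator as supportive, among girls who report the behaviour at baseline.
- Restate the Aim 2 power for the leading measure, with the direction of the ratio and the matching absolute differences made consistent.

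Cost: protocol wording and slightly more analysis. Behaviour is already collected at baseline and every six months, so no new data are needed. The downside is lower power than the decrease indicator if the intervention changes only girls already at risk, which is the reason to keep that indicator as supportive.

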**F. Procedures**

**1. Study Procedures**

A. See Appendices 1 and 2. As described above, The District AIDS Action Committees (DAACs) in Zimbabwe will refer potential participants to our study, and study staff will recruit from public venues. If an individual is interested in participating, and consents to the study, she will sign the consent form and undergo a short self-administered screening questionnaire to determine eligibility. She will also undergo pre-test counseling for HSV-2, HIV and pregnancy, conducted in private at the family health or mobile clinics, and provide blood spots for HIV testing, intravenous blood for HSV-2 testing, and urine for pregnancy testing. Results will be provided within 15 minutes in the context of post-test counseling for HIV and pregnancy. Participants will return within 10 days for HSV-2, and their enrollment visit. Anyone who tests positive for any of these outcomes is ineligible, and will be referred to youth friendly services for clinical care in her area. If the participant’s results are indeterminate, intravenous blood will be used for confirmatory testing using HIV PCR, the results of which will be available within 10 days. She will not be enrolled until the results have been finalized. Participants will also complete a baseline interview (ACASI) at enrollment.

Participants will be randomized at enrollment to one of the two study arms. Details of activities within the two groups are described below, however the main difference is that the participants in the intervention group will also receive vocational training, end of training completion bonus, and career counseling. All other activities will be exactly the same for both groups.

**Prevention for Positives Cohort:** The study procedures for the main study also apply to the new cohort of 50 with the exception that those who positive for pregnancy will still be ineligible while those positive for HIV or HSV-2 will not be excluded. Pregnancy positives will be counseled and referred to the national system for care and follow up.

Specific minor changes that will be made to address the special needs of positives include:

- Revision of counseling scripts and supplemental training for nurses and other staff on issues related to HIV and youth, best clinical practices, confidentiality, stigma and social support, etc.
- Offer volunteer support groups for infected/affected participants, or ensure referral to existing groups in area

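### The Aim 2 comparison of follow-up risk-behaviour prevalence names no baseline term, which costs precision, mainly for sexual debut

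*Protocol*

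**What the plan says.** The Data Analysis section of the protocol sets out two analyses for Aim 2.

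- The first uses the baseline answer: "Changes will initially be computed as binary indicators of decrease in behavior between the initial and final visit", with "results assessed via the between-arm difference in proportions". For clustering, "GEE methods will be used to account for potential correlations between outcomes within peer groups".
- The second is the subject of this point: "We will compare absolute prevalence of risk behaviors at successive follow-up visits in a similar fashion". No baseline term is named for it.

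The baseline answer exists. Under Study Procedures: "Participants will also complete a baseline interview (ACASI) at enrollment". Aim 2 lists as examples of its outcomes "unprotected sex, number of partners, transactional sex, early sexual debut, sexual coercion and violence", so sexual debut is among them. On how many girls may be past debut at entry, the only guide is the pilot: "Among the 50 enrolled in the pilot intervention, 43% had ever had sex".

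**The concern.** A comparison of follow-up prevalence without the baseline answer leaves the differences between girls that existed before randomisation in the error term. Randomisation is not described as stratified by sexual experience, so a chance difference between the arms at entry also passes into the follow-up contrast.

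Debut is the sharpest case. Having ever had sex cannot reverse, so the decrease indicator cannot show an effect on debut. That leaves the follow-up prevalence comparison as the only stated Aim 2 analysis that could. Taken over all girls, it includes those whose outcome was settled before they joined. They dilute the difference and add variance. At stake is whether the trial makes proper use of limited information on an outcome it names.

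**Working it through.** **Inputs**

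- Evaluable girls: 150 per arm less 20% loss = 120 per arm (sample-size section).
- Groups: 150/25 = 6 per arm, so 120/6 = 20 evaluable girls per group; between-group coefficient of variation k = 0.2 (sample-size section).
- Share sexually active at baseline: b = 0.43 (pilot findings).
- New debut among control girls not yet active: q0 = 20-50%. Assumed; the protocol gives no rate.
- Effect among those girls: ratio 0.55 or 0.70, so q1 = ratio × q0. Assumed. The values are borrowed from the Aim 2 sample-size paragraph, where they describe the decrease indicator.
- Two-sided 5% level (sidedness assumed).

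**The plan's own figure.** There is none to reproduce. The stated Aim 2 power refers to the decrease indicator, not to follow-up prevalence or debut.

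**Dilution.** Over all girls, p = b + (1 − b)q. The visible difference is (1 − b)(q0 − q1) = 0.57 × (q0 − q1), that is, 57% of the effect in girls who could still debut.

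**Power for debut, ignoring clustering.** Power = Φ[(d − 1.96·SE0)/SE1], where SE0 uses the pooled proportion and SE1 the separate ones. Example with q0 = 0.30 and ratio 0.55:

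- All girls: p0 = 0.601, p1 = 0.524, n = 120 per arm, d = 0.077, SE0 = SE1 = 0.064. Power 22.3%.
- Girls not active at baseline: 0.300 against 0.165, n = 0.57 × 120 = 68.4 per arm, d = 0.135, SE0 = 0.072, SE1 = 0.071. Power 46.3%.

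| q0 | Ratio 0.55: without / with baseline (share kept) | Ratio 0.70: without / with baseline (share kept) |
|---|---|---|
| 20% | 12.2% / 30.5% (0.40) | 7.6% / 15.2% (0.50) |
| 30% | 22.3% / 46.3% (0.48) | 12.4% / 22.5% (0.55) |
| 40% | 36.9% / 62.6% (0.59) | 19.3% / 31.5% (0.61) |
| 50% | 55.0% / 77.7% (0.71) | 29.1% / 42.6% (0.68) |

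The share kept runs from 0.40 to 0.71, a loss of about 30-60%.

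**With clustering.** Simulation: 12 groups of 20, k = 0.2, identity-link GEE with robust errors and a t reference on 10 degrees of freedom, ratio 0.55, 4,000 runs per setting. At q0 = 20/30/40%, power was 11/18/30% without the baseline covariate and 25/34/47% with it. A second simulation under the same assumptions gave 12/19/32% and 26/38/50%. The share kept is 0.44-0.65 in the first and 0.46-0.64 in the second. Rejection under the null stayed near 5%.

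**Sensitivity**

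- If b = 0.20, the closed form keeps 0.54-0.89 of the power, a loss of 11-46%. In the clustered simulation the gain falls to about 12-14 points.
- If b = 0.43 but 15% of experienced girls under-report (assumed), the gain falls to roughly 2-12 points.

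**Other behaviours.** With baseline-to-follow-up correlation r, adjusted power ≈ Φ[δ/√(1 − r²) − 1.96], where δ is the unadjusted standardised effect. Starting from 80% power:

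- r = 0.2 gives 82%
- r = 0.3 gives 84%
- r = 0.5 gives 90%

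This form ignores clustering and is the more generous. The simulations gave 1-3 points at r = 0.3. At r = 0.5 they gave 4-6 points with k = 0.2 and 4-9 with k = 0.

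**Chance imbalance.** The between-arm SD of baseline sexual experience is √(2 × 0.43 × 0.57/150) = 0.057. A gap of 8 points or more in either direction (0.08/0.057 = 1.40 SD) arises in about 16% of trials.

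**The case against.** The strongest reply is that silence is being read as exclusion. The sentence neither names nor rules out a baseline covariate, and covariate lists and denominators are often left to an analysis plan, which is not shown here. The lead Aim 2 analysis already uses baseline, and the stated power rests on that one. Debut appears only in a list of examples, with no definition and no stated denominator. The debut rate and effect ratio are assumed, self-reports may be inconsistent, and debut power stays well below 80% after the change (25-50% in the clustered simulations at 20-40% debut).

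Most of this stands as a limit on the point's weight. A reader might infer that the protocol forbids baseline adjustment, that the comparison is biased, that every behaviour loses meaningful power, or that debut loses half. The documents support none of these as flat statements. The text is silent rather than prohibitive, and randomisation keeps the contrast unbiased. No correlation is given from which to show a loss on every behaviour. A loss of about half belongs to only part of the assumed range. The pilot's 43% may also be too high here, because the main trial excludes girls who are HIV-positive, HSV-2-positive or pregnant.

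What the reply does not remove is the position of debut. It is a named outcome that one stated analysis cannot address and the other, as worded, addresses inefficiently. Low power after the change is a reason not to discard information already collected.

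**Conclusion.** The point holds as one of efficiency in a further secondary analysis. Its weight lies in debut, where the 30-60% loss rests on the pilot's baseline figure, the assumed debut rate and effect ratio, and consistent reporting. For other behaviours it is a small improvement at almost no cost, of a size the protocol's figures cannot fix. It does not touch Aim 1 or the decrease analysis. The change is worth making.

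**What to change.** Replace the sentence in the Data Analysis section with wording such as: *Prevalence of each risk behaviour at follow-up visits will be compared between arms by GEE, with the participant's baseline value of the same behaviour (enrolment ACASI) as a covariate. Sexual debut will be compared among participants who reported at baseline that they had never had sex.* Keep the planned peer-group clustering, and tabulate the unadjusted prevalences alongside. Interview and randomisation both take place at enrolment, so the text should also say that the baseline answer is taken before allocation is known.

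The cost is a short change of wording and one covariate per model, with no new data or participants. There are two small downsides. Missing baseline answers need a code, and the debut analysis uses only the girls with no prior sex at baseline (about 57% at the pilot figure), who carry all the information on debut.
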